### Data collection

During recruitment to the study, participants will be asked to read and sign a consent form. They will also receive necessary study materials: a smartband, along with instructions on how to connect it to their phones, and their individual study code to enter upon logging in to the app.

The research project is based on the principle of complete anonymity, which means that personal data allowing the identification of users is not obtained. For study participants, detailed information about the anonymity of data and how it is processed and stored can be found in the ‘Privacy Policy’ contained in the application and in the ‘Terms and Conditions of Service’. The only demographic data entered into the application are gender, age, and size of place of residence - data we need to create a lapse risk prediction model. The analysis is entirely anonymous - the user will not be compared with the results of any specific user. We plan to conduct comparisons between large groups of users, but these will never be analyses of individual users. Without the user’s explicit consent, we do not share the collected data with entities other than those directly involved in conducting the research and those to which the provision of data will result from a legal obligation. Unless the research participant decides otherwise, the results will be deleted or left in an anonymized form within 30 days from the end of the last phase of the study.

Ecological data will be gathered through a mobile application installed on the participants’ smartphones. Upon initial access, participants will encounter a baseline questionnaire designed to collect demographic data and information regarding their patterns of substance use. Throughout the study’s duration, participants will respond to daily EMA prompts and complete a series of questionnaires at specific timepoints, as delineated in **Figure 1**. Throughout the course of the study, the app will be sending daily reminders about EMA prompts, to enhance compliance.

**Figure 1 f1:**
[figure not shown]
Flowchart of the study design.

In conjunction with the mobile app data collection, participants will be equipped with smartbands to monitor various physiological parameters, including sleep duration and quality, heart rate, and physical activity levels.

To bolster participant retention rates, an incentive in the form of a contest has been integrated into the study. Participants will be invited to share their experiences with the Nałogometr app, specifically how it aids in modifying their substance use behaviors. The prizes for this contest include a smartwatch and gift cards from the popular polish bookstore, Empik. This motivational component is anticipated to enhance participant engagement and adherence to the study protocol.

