### Study design

The study was pre-registered within the Open Science Framework (OSF) repository: https://osf.io/z4xqd.

A two-arm participant-blinded randomized control trial will be conducted via a mobile app. The study will compare an intervention experimental condition with a waitlist control condition.

Throughout the duration of the study, participants assigned to the experimental group will have access to self-guided psychological interventions.

Participants will be asked to complete daily EMA questions, as well as questionnaire battery assessments at multiple timepoints: 1) at baseline – in the first week, following onboarding questionnaire; 2) after one month; 3) after two months; 4) after three months.

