### Randomization

Upon their initial login to the mobile application, participants in each group (alcohol, cross-addiction, and cannabis), will be randomly allocated to either the experimental or control condition based on a code they receive during recruitment. Codes corresponding to experimental and control conditions were generated seperately for each group and then put in a randomized sequence. The randomization was done via an online randomization tool (45. [Online] Available from: https://www.sealedenvelope.com/simple-randomiser/v1/lists). Block sizes were determined using the simulation tool (45. [Online] Available from: https://www.sealedenvelope.com/randomisation/simulation/, taking into account planned sample sizes. Participants assigned to the experimental condition will gain immediate access to all psychological interventions following their initial app login. Those in the control condition will have access only to the daily EMA questions and the sobriety calendar, a tool for tracking their substance use. They will be provided access to the complete version of the app, including the psychological interventions, subsequent to the study’s conclusion - which is scheduled for 98 days after the first login.

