### Procedure

The study will be conducted with the use of *Nałogometr 2.0*, a mobile app designed to reduce craving and lapse risk in SUD and enhance post-treatment effects (available freely on Google Play and App Store). Prior to the first login, participants will be automatically navigated through all the necessary permissions and consents regarding data collection. Following the app installation, participants will be prompted with an onboarding questionnaire to collect demographic data. They will have a one-week window to complete the initial standardized questionnaire battery assessment. The responses from this initial assessment will serve as the baseline for subsequent evaluations throughout the study. The schedule of these assessments is outlined in **Figure 1**.

During a three-month period, participants will be required to engage in daily EMA assessments and to complete a monthly questionnaire battery. Concurrently, physiological data will be continuously gathered via smartbands.

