Regarding the limitations of the study, we anticipate the potential for a high dropout rate, a common occurrence in previous studies (42) and a concern intrinsic to trials with a longitudinal design. Nonetheless, the inclusion of a contest as an engagement strategy is expected to enhance participant retention rates. It’s crucial to note that the opportunity to win prizes is independent of participants’ self-reported levels of craving or instances of lapses, thereby mitigating any potential bias in their responses.

Drop-out rates in mobile application studies on addiction can be high due to various factors, including lack of motivation, technical issues, limited support and guidance, loss of interest, or intervention design. Lack of adequate support, guidance, or encouragement from researchers or healthcare professionals throughout the study can diminish users’ motivation and commitment to using the application. Reducing dropout rates in mobile applications designed for addiction research requires a combination of strategies to increase engagement and enhance the intervention’s effectiveness. Behavioral tracking and personalized feedback can help users stay motivated and focused on their goals. We will use push notifications and reminders to prompt users to engage with the application regularly, complete tasks, or provide updates. We also provide educational materials and psychological intervention modules based on CBT and mindfulness techniques, which could increase the retention rate and provide support in coping with substance use disorder. We informed users at the beginning of the study that the application could not replace psychotherapy.

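### The trial is called participant-blinded although controls get a visibly reduced waitlist app; with self-reported primary outcomes, expectancy bias cannot be excluded, and the retention contest adds a cue that presumes benefit.

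*Protocol article*

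**What the plan says.** **Blinding and comparator.** Under Study design: "A two-arm participant-blinded randomized control trial will be conducted via a mobile app". The next sentence reads: "The study will compare an intervention experimental condition with a waitlist control condition".

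**What each arm sees.** Under Randomization, for the experimental arm: "Participants assigned to the experimental condition will gain immediate access to all psychological interventions following their initial app login". For the control arm: "Those in the control condition will have access only to the daily EMA questions and the sobriety calendar". Controls get the rest later: "They will be provided access to the complete version of the app, including the psychological interventions, subsequent to the study", with the end of the study set at 98 days after first login. Mobile application content repeats that controls lack the app's full functions until then. Procedure describes the app as "available freely on Google Play and App Store".

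**Outcomes.** Primary outcomes names the number of lapses and momentary craving, both reported by the participant.

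**Contest.** Data collection (text after Figure 1) describes a retention contest with a smartwatch and gift cards as prizes. Participants are invited to share their experience of the app, "specifically how it aids in modifying their substance use behaviors". The invitation is not limited to one arm. The Discussion argues that the chance of a prize does not depend on reported craving or lapses, "thereby mitigating any potential bias in their responses".

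**The concern.** Blinding of participants protects a self-reported outcome because neither arm knows whether to expect benefit. Here one arm opens an app full of exercises and the other opens a diary and a calendar, with the full version promised later. Participants who can tell which version they hold may report craving and lapses differently for that reason alone. With no objective measure of substance use described (the smartbands record sleep, heart rate and activity), such a shift in reporting could not be told apart from a treatment effect.

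The label matters in its own right. A reader who sees participant-blinded will tend to set this source of bias aside. The contest then asks for accounts of how the app helps with the very behaviour that the primary outcomes measure. The limitations in the Discussion cover dropout and small effects. They mention response bias only to say that the prize rule mitigates it, and do not mention expectancy.

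**Working it through.** **1. Does the stated design support the label?** Setting the sections side by side:

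| Feature | Experimental arm | Control arm | Section |
|---|---|---|---|
| Intervention modules during the study | all, from first login | none | Randomization |
| EMA questions and sobriety calendar | yes | yes, and nothing else | Randomization; Mobile application content |
| Full app | at once | after 98 days | Randomization |
| Sham or attention-matched content | – | none described | – |

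The comparator is named as a waitlist, the difference in content is visible on screen, and the full app can be found in public app stores. The article describes no means by which participants would be kept unaware of their condition. The label is therefore a stated property that the described design does not have.

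**2. What does the argument about prizes cover?** It says that reporting less craving or fewer lapses does not improve the chance of winning, so there is no direct payment for favourable scores. It does not address the leading wording of the invitation, or expectations that arise from seeing one's own version of the app.

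**3. Does the contest act differently in the two arms?** The text does not establish this. Both arms may enter. Controls can write about EMA and the calendar, and the Introduction itself treats self-monitoring as helpful. The experimental arm has more content to write about, but a difference in effect on reporting or retention is an inference.

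**4. Illustration of scale.** The plan states no bias figure to reproduce. Its minimum of 360 participants for 80% power comes from a simulation whose numerical inputs are not given, so that figure can be neither reproduced nor refuted here.

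Inputs: 180 per arm (360/2, Sample size calculation); two-sided alpha of 5% (assumed); outcome SD of 1 and a single measurement (assumed); no true effect; a between-arm reporting shift of b SD (assumed).

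- SE = sqrt(2/180) = 0.1054.
- Difference detectable with 80% power = (1.960 + 0.842) × 0.1054 = 0.295 SD.
- Rejection rate = Φ(b/SE − 1.96) + Φ(−b/SE − 1.96).

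| Assumed b (SD) | b/SE | Two-sided rejection rate | b as share of 0.295 |
|---|---|---|---|
| 0 | 0 | 5.0% | 0% |
| 0.05 | 0.474 | 7.6% | 17% |
| 0.10 | 0.949 | 15.8% | 34% |
| 0.15 | 1.423 | 29.6% | 51% |

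Participants plans for about 400 (150 + 150 + 100). With 200 per arm the last three rates become 7.9%, 17.0% and 32.3%. These figures show only that a modest shift matters when the effect sought is small. They say nothing about whether a shift will occur.

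**The case against.** The strongest reply has four parts.

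- **Blinding.** The consent wording and Figure 1 are not shown. Controls may not have been told about the modules, in which case some masking is conceivable. This stands to the extent that the article should then say what was concealed. It does not rescue the label as written, because a waitlist is named and no masking method is given.
- **Contest.** The article summarises it in a few sentences. The actual prompt, judging rules and timing are not shown, and both arms may take part. This stands. A reader might infer that the contest favours the experimental arm, or keeps more of that arm in the study. The documents do not support that as a fact.
- **Existing protection.** Prizes are independent of the outcomes, and data collection is described as anonymous, which weakens any motive to please. Both reduce the risk. Neither removes expectancy.
- **Magnitude.** The shifts are assumed. The benchmark is a single-measure comparison, whereas the plan uses a mixed model with random intercepts, and an SD shift does not map directly onto a count of lapses. This also stands. A reader might take the table as an estimate of the trial's type I error, and it is not one.

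**Conclusion.** The point holds in this form. The participant-blinded label is at odds with the waitlist design in the same article, and because both primary outcomes are self-reported, expectancy bias that differs by arm cannot be excluded. The contest wording adds a cue that presumes benefit, and the argument about prizes answers only the direct incentive to misreport.

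The size and direction of any bias, and any difference between arms in the contest's effect, cannot be derived from the documents; the error rates above are illustration under assumed shifts. The conclusion rests on one inference, that participants can recognise their version of the app. The described content and the app's public availability make that likely, but the missing consent wording leaves it unproven. This should be corrected, mainly so that readers weigh the self-reported results properly. It does not by itself invalidate the comparison.

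**What to change.** 1. In Study design, describe participants as not blinded, or state exactly what was concealed from them and how.
2. In the limitations part of the Discussion, list expectancy and self-report bias, and say that the prize rule removes only the direct incentive to misreport.
3. Keep the same prizes, but award them under identical rules in both arms for completing assessments (for example, by lottery), or else make the contest prompt neutral. Collect any accounts of experience only after each participant's own follow-up ends, at day 98 after first login.

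A question asking participants to guess their allocation is not needed: if allocation is visible it tells little, and late in follow-up the answer is mixed with perceived benefit.

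**Cost.** The design label becomes less favourable, and the changed contest needs an ethics notification. A prize tied to completion carries some risk of perfunctory EMA entries. If enrolment has begun, earlier and later participants would have different incentives, which should be reported. In that case items 1 and 2 can still be done at almost no cost. Arms, sample size and intervention are unchanged.

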### Randomization

Upon their initial login to the mobile application, participants in each group (alcohol, cross-addiction, and cannabis), will be randomly allocated to either the experimental or control condition based on a code they receive during recruitment. Codes corresponding to experimental and control conditions were generated seperately for each group and then put in a randomized sequence. The randomization was done via an online randomization tool (45. [Online] Available from: https://www.sealedenvelope.com/simple-randomiser/v1/lists). Block sizes were determined using the simulation tool (45. [Online] Available from: https://www.sealedenvelope.com/randomisation/simulation/, taking into account planned sample sizes. Participants assigned to the experimental condition will gain immediate access to all psychological interventions following their initial app login. Those in the control condition will have access only to the daily EMA questions and the sobriety calendar, a tool for tracking their substance use. They will be provided access to the complete version of the app, including the psychological interventions, subsequent to the study’s conclusion - which is scheduled for 98 days after the first login.

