### Participants

The research will be conducted in collaboration with MONAR and AKMED, Polish organizations responsible for overseeing numerous addiction treatment clinics and centers, as well as other independent institutions. Recruitment of participants will target clinical patients who are undergoing either in-patient or out-patient treatment for Substance Use Disorder (SUD). For the in-patient cohort, the study will include individuals who are in the final stage of their therapy, specifically those expected to conclude their treatment within a maximum of 4 weeks but not fewer than 5 days. Eligible participants must be adults, aged 18 years or older, and must possess fluency in Polish. Moreover, in light of the study’s methodology, enrollment will be limited to users of iOS or Android smartphones.

Participants will be recruited into three groups: 1) Patients with alcohol addiction, 2) Patients with cross-addiction (alcohol and stimulants), 3) Patients with cannabis addiction. We plan on recruiting 150 participants with alcohol addiction, 150 participants with cross-addiction, and ~100 participants with cannabis addiction, due to lower availability of CUD therapeutic programs in Poland – and subsequently, less patients finishing therapy.

Each participant will be assigned to either experimental or control condition upon logging in to the mobile app for the first time.

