### Sample size calculation

A simulation-based power analysis was performed to determine the sample size, premised on the use of a linear mixed-effects model with subject-level random intercepts and a small effect size of the intervention. This effect size assumption was informed by literature on the efficacy of mobile interventions in mitigating addictive behaviors (for a review, see 25). The simulation indicated that a minimum of 360 participants would be necessary to achieve an 80% power threshold for detecting a significant group effect. The sampling strategy has been devised to capture maximal demographic variance within the sample, with particular attention to characteristics such as gender, age, geographic location, and socioeconomic status.

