### Data analysis

Factorial design mixed-effects models will be applied to compare questionnaire battery scores between experimental groups and the control across measurements. In addition, we will perform an interrupted time series analysis to estimate the effects of different types of interventions on longitudinal ecological momentary assessment outcomes.

In the statistical analysis, we will incorporate data from participants who have completed a minimum of 21 Ecological Momentary Assessment (EMA) entries, spread over the one-month period dedicated to evaluating the intervention. For the assessment of the intervention’s enduring effects, the analysis will consider participants who have logged at least three EMA entries during the follow-up phase. In addition, within the intervention group, we will include those who have accessed the app and engaged with the self-guided intervention modules on a minimum of four occasions and at least once, respectively; this will represent the minimal therapeutic exposure required for the study. For the analysis of secondary outcomes, we will include participants who have completed the initial baseline assessment as well as at least one subsequent follow-up assessment.

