## Discussion

In this protocol, we detail the framework for a two-arm randomized controlled trial aimed at evaluating the efficacy of CBT and mindfulness-based mobile intervention modules administered through the Nałogometr 2.0 app. The objective is to ascertain the impact of these mobile interventions in mitigating cravings and lapses associated with SUD. By examining the utility of the interventions across clinical populations with distinct addiction profiles—alcohol, cannabis, and mixed (alcohol and stimulants) addiction—we aim to gauge the effectiveness of the intervention modules for various manifestations of SUD.

Patients with SUD face a high risk of relapse post-treatment, with estimates suggesting that 40-80% of individuals relapse into addiction following the conclusion of therapy. Mobile psychological intervention modules stand as a potentially powerful means of supporting patient recovery and enhancing the long-term outcomes of treatment. Should the interventions prove effective, they could make a significant contribution to the domain of addiction therapy, representing a valuable asset in the ongoing effort to prevent lapses and relapses.

Furthermore, the study will encompass exploratory analyses aimed at discerning whether the efficacy of the interventions correlates with user engagement levels within the app and subsequent alterations in other psychological domains, such as impulsivity, sensation seeking, stress management, and emotion regulation. These analyses will also consider physical functioning indicators collected through physiological metrics, including heart rate, sleep quality, and activity levels. Delving into this ancillary data will provide deeper insights into the recovery mechanisms from SUD and could inform the enhancement of future health interventions for addictive disorders.

The proposed randomized controlled trial (RCT) will focus on a post-therapy clinical patient population—a demographic that is particularly susceptible to relapse. Conducting the study within the naturalistic settings of the patients ensures the ecological validity of the results and the derived conclusions. Through the collection and analysis of longitudinal data over a span of three months, complemented by regular monthly follow-up assessments, the research aims to elucidate the dynamics of post-therapeutic shifts in cravings and behaviors in patients with SUD.

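### Randomisation is stratified by addiction group, but neither the sample-size model nor the stated arm comparison names that stratum; comparisons of arm levels would then be mildly conservative

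*Protocol article*

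**What the plan says.** - **Randomization.** Within each addiction group, participants are "randomly allocated to either the experimental or control condition", and "Codes corresponding to experimental and control conditions were generated seperately for each group". Block sizes were chosen with the planned group sizes in mind. This is stratified, blocked randomisation.
- **Participants.** "We plan on recruiting 150 participants with alcohol addiction, 150 participants with cross-addiction, and ~100 participants with cannabis addiction".
- **Sample size calculation.** The simulation was "premised on the use of a linear mixed-effects model with subject-level random intercepts and a small effect size of the intervention". It found that "a minimum of 360 participants would be necessary to achieve an 80% power threshold for detecting a significant group effect". No stratum term is mentioned.
- **Data analysis.** "Factorial design mixed-effects models will be applied to compare questionnaire battery scores between experimental groups and the control across measurements". The factors of the factorial model are not listed. Outcomes from the daily assessments go to an interrupted time series on types of intervention, again with no mention of addiction group.
- **Discussion.** Looking across the three addiction profiles, "we aim to gauge the effectiveness of the intervention modules for various manifestations of SUD". No model is attached to this aim.
- **Measures, Randomization and Procedure.** Substance-use history is collected at first login. Module access in the experimental arm starts at that login, while the baseline questionnaire battery may be completed up to a week later.

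**The concern.** Stratified allocation balances the arms within each addiction group, so differences between groups no longer add to the sampling error of the arm contrast. A model without the stratum still counts those differences as residual noise. Its standard error is then larger than the real one, its test runs below the nominal level, and part of the precision bought by stratifying is lost.

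The groups are defined by substance, and Table 1 gives the AUDIT to all three, cannabis patients included. Outcome levels could therefore plausibly differ by group. The effect-by-type aim depends on the same term: without addiction group in the model there is no pooled test of whether the effect differs by type.

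**Working it through.** **1. The plan's own figure.** N = 360 can be neither confirmed nor refuted, because the article gives no numerical effect size, alpha, number of measurements or within-person correlation. Assume d = 0.2, 5% two-sided and one measurement: n per arm = 2 × ((1.96 + 0.842)/0.2)² ≈ 393, or 786 in total (620 one-sided). With one measurement, 360 gives 80% power at d = 2.802 × √(2/180) = 0.295. With four measurements at d = 0.2, the factor (1 + 3ρ)/4 must equal 180/392.4 = 0.459, so ρ = 0.28. The stated 80% at N = 360 is taken as the starting point below.

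**2. Arm-level contrast, stratum omitted or included.** Inputs: 1:1 allocation (ratio not stated), 5% two-sided (not stated), balance within strata, and an 80% calculation that used the total variance. R² is the share of variance in the analysed participant-level outcome explained by addiction group. The documents give no R², so a range is shown.

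- True SE = √(1 − R²) × the SE reported without the stratum
- True alpha, stratum omitted = 2(1 − Φ(1.96/√(1 − R²)))
- Power, stratum omitted = Φ(0.842/√(1 − R²))
- Power, stratum included = Φ(2.802/√(1 − R²) − 1.96)

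| Assumed R² | SE too wide by | True alpha | Power omitted | Power included | Points lost |
|---|---|---|---|---|---|
| 2% | 1.0% | 4.8% | 80.2% | 80.8% | 0.6 |
| 5% | 2.6% | 4.4% | 80.6% | 82.0% | 1.4 |
| 10% | 5.4% | 3.9% | 81.3% | 84.0% | 2.7 |

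For R² = 10%: 1.96/√0.9 = 2.066, so alpha = 3.9%; 2.802/√0.9 − 1.96 = 0.993, so power = 84.0%.

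**3. Simulation check.** 400 participants in strata of 150/150/100, balanced within stratum, 8,000 runs per setting. At R² = 10%, type I error was 4.0% without the stratum and 5.3% with it, mean SE 0.100 and 0.095, power 81.0% and 83.6%. At R² = 5%, type I error was 4.7% and 5.3%, power 81.4% and 82.7%. With a Monte Carlo standard error of about √(0.05 × 0.95/8000) = 0.24 points on type I error, this agrees with the formulas.

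**4. Change-from-baseline contrast.** In a random-intercept model with complete data, a constant difference between addiction groups sits in the participant intercept and cancels from the arm-by-time term. Illustration with assumed variances: between-person 0.5 (of which stratum 0.2), residual 0.5, four visits, 200 per arm.

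- Arm-by-month-1 term: SE = √(2 × 0.5 × 2/200) = 0.100, with or without the stratum.
- Arm main effect: participant-mean variance = 0.5 + 0.5/4 = 0.625, so SE = √(0.625 × 2/200) = 0.079. With the stratum in the model it is √(0.425 × 2/200) = 0.065.

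A simulation of this design (40 runs) gave the same values: 0.0999 both ways for the interaction, and 0.079 against 0.065 for the main effect. Simulated type I error of the change contrast without the stratum was 4.8% to 5.6%.

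**5. Why effects by type should be exploratory.** With 75, 75 and about 50 per arm and one measurement (SD 1, 1:1), the 95% interval half-width is 1.96 × √(2/75) = 0.32 in the two larger groups and 1.96 × √(2/50) = 0.39 in the cannabis group. Both exceed the 0.295 from step 1.

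**The case against.** The strongest reply is that the article is silent, and silence is not omission. The factors of the factorial model are not listed, addiction group may be one of them, and a condensed article usually leaves model terms to the SAP. This stands: a reader might infer that the stratum has been left out, but the text does not say so. What remains is a recommendation that the analysis follow the randomisation.

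The second reply is that the primary hypothesis concerns reduction relative to baseline, and step 4 shows that such a contrast needs no stratum term. This also stands, unless addiction group predicts change over time. It does not cover the powered group effect if that means an arm main effect, nor a comparison of craving levels or lapse counts.

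The third reply is that the interrupted time series concerns types of intervention and is not stated as an arm comparison. That is right; the absence of a stratum term there is no mismatch with the randomisation.

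Three further inferences are tempting and unsupported:

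- That intervals are too wide because onboarding data are not adjusted for. Those variables were not balanced by design, so the unadjusted standard error is valid and only less precise.
- That the onboarding data go unused. The article says they are collected and nowhere excludes them from analysis.
- That three separate subgroup tests are planned. The Discussion states an aim and proposes no such tests.

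**Conclusion.** The point holds in limited form. Allocation is stratified, and neither the sample-size model nor the stated arm comparison names the stratum. For comparisons of arm levels, omitting it would cost about 1.4 to 2.7 points of power and take a 5% test to about 4.4% to 3.9%, if addiction group explains 5% to 10% of the outcome variance. That share, the 5% two-sided level and 1:1 allocation are assumptions. The formulas are for a linear comparison and are only a guide for lapse counts.

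The error is conservative: it adds no bias and does not inflate type I error, and on these figures power without the stratum stays at or above the planned 80%. A change-from-baseline contrast is essentially untouched. It is worth correcting because the remedy is nearly free, not because the trial's conclusions are at risk.

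**What to change.** 1. Include addiction group (three levels) as a fixed effect in the arm comparisons of craving, lapses and questionnaire scores.
2. For the aim in the Discussion, fit one arm-by-group interaction in the pooled model. Report group-specific estimates with confidence intervals, labelled exploratory.
3. Optionally, add a prespecified onboarding covariate recorded at first login, for precision only. The baseline battery is less safe as the sole covariate because it may be completed up to a week after module access. On the included-power formula in the working, with r² in place of R², an assumed correlation of 0.3 or 0.5 with the outcome would raise 80% power to about 84% or 90%. Define the covariate with care: frequency of use is not on one scale across the groups, and abstinence length in in-patients may partly reflect length of stay.

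The cost is analysis wording and two extra model parameters for the stratum, plus two for the interaction model. No new data are needed. The Data analysis section also restricts the analysed sample by completed assessments and, in the intervention arm, by app use, so balance within strata is not guaranteed there. The stratum term would correct a resulting imbalance in addiction-group mix, though not the selection itself.
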